#### Control group

Patients in the control group will receive traditional core stability training and conventional rehabilitation therapies. Routine rehabilitation training will include drafting training, passive joint movement, walking between parallel bars, and occupational therapy, among others. At the same time, core stability training will include abdominal training in the supine position, double-bridge movements, single-bridge movements, balance ball half-bridge movements, and forward and backward movement of the sitting pelvis. The patient will be sat on a Bobath ball and use the Bobath handshake to control the flexion, extension, lateral flexion, and rotation of the torso. Before the training begins, the therapist will inform the patient of the brief action instructions. For patients with poor respiratory control, manipulation will be adopted to stimulate their abdominal muscle group contraction, and necessary manipulation should be undertaken according to the different limb functions of the patients. The duration of conventional rehabilitation training will be five times per week, 30 min per session, lasting for 2 weeks. The traditional core stability training will last for 15 min, five times per week, for 2 weeks. All of the control group interventions for traditional core stabilization training will be performed separately by three experienced therapists.

#### Study group

In addition to receiving conventional rehabilitation training, patients in the study group will be required to complete the LQG treatment. Patients allocated to the study group will be engaged in LQG rehabilitation programs in addition to conventional rehabilitation therapies. The sequence will be routine rehabilitation and then core stability training. Each time, the rehabilitation course will be divided into LQG for 15 min and normal rehabilitation training for 30 min. The study group will complete training five times per week for 2 weeks in a quiet room. For traditional core stabilization training, all study group interventions will be performed separately by three experienced therapists.

The key points of LQG oral guidance will consist of pronunciation and breathing. For “xu,” pronunciation will be assisted by the teeth. Space will be left between the teeth and the tongue, with the upper and lower teeth parallel. Air will be drawn from the space between the teeth, as well as between the teeth and the tongue, and the corners of the mouth will be pulled back a little. When exhaling and pronouncing, the “he” will be pronounced with the aid of the tongue. The upper teeth will be tapped with the sides of the tongue and air exhaled between the tongue and the upper jaw. During the exhalation and pronunciation, the “hu” sound will be assisted by the throat. The sides of the tongue will be bent upward and the lips forward, forming a circular opening through which the patient will exhale. During exhalation and pronunciation, the “si” will be pronounced with the assistance of the teeth. There will be a narrow gap between the upper and lower teeth. The patients will lightly touch their lower teeth with the tip of their tongue and exhale air between their teeth. During the exhalation and pronunciation, the “chui” will be pronounced with the assistance of the lips. The tongue and the corner of the mouth will be pulled back, as will the lips into the stretched position, making the back teeth parallel and thus exhaling air from the throat between the sides of the tongue and the stretched lips. In the exhalation process, the “xi” will be pronounced with the assistance of the teeth. The lower teeth will touch the tip of the tongue, and the corners of the mouth will be slightly tilted back, the posterior teeth gently closed, and air exhaled through the space between the posterior teeth [30–32].

Our training is a one-to-one intervention delivered by the therapist. Before training, for the elderly, we will tell each patient that the emphasis will be on breathing and pronunciation. In order that the patient should learn correct pronunciation and breathe accurately, the patient will need to learn gradually to “feel” the key points of strength rather than the absolute power of pronunciation. For example, the patient may complete the training in a sitting or standing position. Stroke patients should learn to use healthy upper limbs to assist upper limb movement. Alternatively, the physiotherapist can stand on the patient’s side to assist in the completion of the movement and maintain the normal position of the chest, spine, and pelvis to provide a stable mechanical structure. Our training is not in the form of group exercises, but in the form of one-to-one therapist intervention.

#### LQG action points

Stroke patients with postural dysplasia often show different degrees of hemiplegia and postural abnormalities, resulting in the loss of their ability to sit or stand. It is impossible for these patients to complete the LiuZiJue key independently and precisely without assistance. Therefore, the therapist will properly guide the completion of the movement and adjust the training position according to the patient’s functional state. As the improvement of patient’s balance ability increases, the training position will gradually transition from the sitting position to an independent standing position. As the patient’s limb function improves, the therapist will gradually reduce the amount of assistance. Both active and auxiliary limb movements are based on bilateral limb opposition. The most important goal is to complete an accurate respiratory guidance program.

#### Sample size calculation

We will use the TIS as the main therapeutic index to evaluate trunk posture control. The preliminary experimental findings showed that the effective rate was 80% in the study group and 50% in the control group. The effective rates of the study group and the control group were set as 80% and 50%, respectively. On this basis, sample estimation was conducted using G*Power 3.1 software, and the rank-sum test was adopted to set the rates of 80% in the treatment group and 50% in the control group for bilateral testing, and we set α = 0.05 and power = 0.97 (the setting of this value is based on the statistical power after the end of the experiment; power = 0.97 after the end of 40 cases). The distribution ratio was matched by 1:1, and the final sample size was set as 142, with 71 subjects in each of the two groups, taking into account the possibility of 12% attrition rate during the study. Therefore, the total number of samples was finally determined to be 160 cases, namely 80 cases in each group.

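### The 0.97 power target rests on an observed power at 40 cases that the stated 80% and 50% rates do not support, and under the plan's own missing-data rule power is about 0.93

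*Protocol article*

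**What the plan says.** All the sizing inputs stand in the protocol article under Sample size calculation. Preliminary findings are reported as follows: "the effective rate was 80% in the study group and 50% in the control group". The same two rates are then adopted for the design, with two-sided testing and 1:1 allocation: "we set α = 0.05 and power = 0.97". The reason for 0.97 follows in brackets: "the setting of this value is based on the statistical power after the end of the experiment", and then "power = 0.97 after the end of 40 cases". A rank-sum test in G*Power is named as the sizing method. The result is "the final sample size was set as 142, with 71 subjects in each of the two groups", raised to 160 (80 per arm) by "taking into account the possibility of 12% attrition rate during the study".

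Three other places bear on the point:

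- Primary outcome measurement procedures grades the TIS change as CR, PR or NR, and Table 1 there schedules the TIS at baseline and 2 weeks.
- Statistical analysis compares efficacy between groups by chi-square and defines an effective rate that pools the two better grades.
- The same section fills missing data by carrying the last observation forward and lets the ITT result prevail if ITT and per-protocol results differ.

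**The concern.** The section gives two sample sizes for one power. It reports 0.97 as already reached at 40 cases, then asks for 142 patients to reach 0.97. If both figures refer to the same rates and the same kind of test, they cannot both be right.

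The logic is also unsound whatever the number. Power computed from a finished experiment's own observed effect restates that experiment's p-value. It says nothing about how much power the next trial should have, and here the same preliminary data supply both the assumed effect and the power target.

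The sizing also treats the 12% as patients who leave the analysis. Under the plan's missing-data rule they stay in the ITT analysis, where they dilute the difference. A reader who takes 0.97 at face value would credit the trial with more power than its deciding analysis has, which matters most if the result is null.

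**Working it through.** **Inputs** (Sample size calculation): p1 = 0.80, p2 = 0.50, two-sided α = 0.05, 1:1 allocation, target power 0.97, loss 12%, 160 randomised.

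**Step 1. Reproduce the 142.** Two proportions, pooled variance under the null, p̄ = 0.65:

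n per arm = [1.960·√(2·p̄·(1−p̄)) + z·√(p1(1−p1) + p2(1−p2))]² / (p1−p2)²

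- √(2·0.65·0.35) = 0.6745 and √(0.16 + 0.25) = 0.6403; z for 0.97 is 1.881.
- n = (1.322 + 1.204)² / 0.09 = 70.9, so 71 per arm and 142 in total. This matches the plan.

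**Step 2. Power at 40 cases, same inputs.** Power = Φ[(0.30·√n − 1.322)/0.6403]:

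| n per arm | 0.30·√n | z | power |
|---|---|---|---|
| 20 (40 in total) | 1.342 | 0.031 | 0.512 |
| 40 (80 in total) | 1.897 | 0.898 | 0.816 |
| 70 | 2.510 | 1.855 | 0.968 |
| 71 | 2.528 | 1.883 | 0.970 |

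The plan does not say whether 40 is the total or the number per arm, so both are shown. Other two-category methods do not rescue the figure:

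| method | 20 per arm | 40 per arm |
|---|---|---|
| exact chi-square | 0.53 | 0.82 |
| arcsine | 0.53 | 0.82 |
| Fisher | 0.41 | 0.75 |
| one-sided | 0.64 | 0.89 |
| t and Wilcoxon approximations | 0.43–0.53 | 0.73–0.83 |

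With the control rate at 50%, power 0.97 would need a study-group rate of about 99% with 20 per arm or 88.5% with 40 per arm.

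**Step 3. Three-grade rank-sum test.** The plan gives no CR/PR split, so these are assumed splits (CR/PR/NR, study v control) that keep the effective rates at 80% and 50%. Power is by simulation:

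| split | 20 per arm | 40 per arm |
|---|---|---|
| 50/30/20 v 30/20/50 | 0.44 | 0.73 |
| 40/40/20 v 10/40/50 | about 0.71 | about 0.95–0.96 |
| 60/20/20 v 10/40/50 | about 0.88 | about 0.99 |
| 70/10/20 v 5/45/50 | about 0.96 | above 0.99 |

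So 0.97 can be reached at 40 per arm under some splits, and with 20 per arm only under very lopsided ones.

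**Step 4. Attrition.** 142 × 1.12 = 159.04, which rounds up to the stated 160. The loss should be divided out: 142/0.88 = 161.4, so 162. From 160, 160 × 0.88 = 140.8 remain, about 70 per arm, with power about 0.97 (Step 2).

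**Step 5. Power under the plan's missing-data rule.** Assume that 12% in each arm are lost before 2 weeks with only a baseline TIS. The carried-forward change is zero, which is neither CR nor PR.

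- Effective rates: 0.88 × 0.80 = 0.704 and 0.88 × 0.50 = 0.440. Difference 0.264, p̄ = 0.572.
- z = (0.264·√80 − 1.960·√(2·0.572·0.428)) / √(0.704·0.296 + 0.440·0.560) = (2.361 − 1.371)/0.674 = 1.468.
- Power = 0.929 at 80 per arm.

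**Step 6. Detectable difference.** At 70 per arm, 72.9% v 50% gives power 0.80.

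**The case against.** The strongest objection is that 0.51 and 0.82 depend on a choice of test. The sizing text names a rank-sum test, the primary outcome is defined as three ordered grades, and nothing says that the 40-case power was computed on the collapsed effective rate. Step 3 shows that a three-grade analysis at 40 per arm can reach 0.97. This stands in part: a reader might infer that 0.97 at 40 cases is impossible, and the documents do not support that. They do not support the figure either, because only the two effective rates are given and the 142 matches the two-category calculation exactly.

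The second objection is that the attrition shortfall is trivial and does not arise in the ITT analysis, where lost patients are retained. Both parts are right. It is a loss of 1.2 patients and about 0.001 of power. The shortfall applies to an evaluable-patient analysis and the 0.93 to the ITT analysis; they are alternatives and must not be added together.

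The third is that 0.93 assumes that every lost patient has only a baseline value. The Abstract and Trial design also mention an assessment at the end of the rehabilitation course, and if that is a separate visit, some patients could carry a 2-week value forward. That stands as a condition on the figure. Against it, Table 1 shows only two time points and the limitations section says that nothing is followed up after the intervention.

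Finally, a high power target makes the trial larger, not smaller, and 0.93 is still good power. This also stands, and it limits the point to what the protocol claims for its sample size.

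**Conclusion.** The point holds as a matter of justification and stated power. For 80% v 50% as two categories, 40 cases give 0.51 or 0.82, not 0.97. The 40-case figure is unsupported as written, and an observed power would not be a valid basis for a target even if it reproduced. The 142 is correct for 0.97. In the ITT analysis, with 12% lost in each arm and only a baseline TIS for those patients, power at 80 per arm is about 0.93.

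A reader might go further and infer that the trial is too small or needs more patients. The documents do not support that: if the assumed rates are true, power is about 0.97 in evaluable patients and about 0.93 in the conservative case. The 162 v 160 discrepancy is a minor slip in method. All these figures assume that the primary comparison is of the effective rate as two categories; the Statistical analysis section does not say whether the chi-square test is applied to that rate or to the three grades.

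**What to change.** Delete the 40-case justification for the power and keep 160. Replace it with a statement of this kind:

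*For the effective rate compared as two categories, 160 randomised gives power about 0.97 for 80% v 50% in about 140 evaluable patients, about 0.93 in the ITT analysis if the 12% lost have only a baseline value and count as no response, and 80% power for about 73% v 50% in evaluable patients.*

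If the sponsor wishes to keep the 40-case figure as background, the text should say whether 40 is the total or per arm, name the test and give the CR/PR/NR split, and should not use the figure to set the target.

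The cost is a change of protocol wording. No patients are added and no planned analysis changes. The downside is that the stated power becomes slightly less favourable.

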### Statistical analysis

In this study, the main indicators were determined according to the change levels of TIS before and after treatment, which were divided into three levels of CR, PR, and NR and expressed by rate or percentage. The chi-square test will be used to compare differences in efficacy between groups. The overall curative effect evaluation and the curative effect evaluation method will be employed. The calculation formula is as follows: Effective = (excellent + effective)/total cases × 100%. Secondary indicators (e.g., MPT, MBI, BBS, FMA, diaphragm thickness and mobility, static and dynamic balance ability) are all continuous data. A paired sample *t* test is often used for intragroup comparison, whereas an independent sample *t* test is often used for intergroup comparison of the difference between the two groups after treatment, and a two-sided test will be used with the significance level set at *P* ≤ 0.05. To eliminate the influence of rehabilitation intervention time, stroke type, age, and gender on the efficacy and relative size of intervention methods will be considered and the statistical method of stepwise logistic regression model adopted.

The intention-to-treat (ITT) group is divided into final analysis set (FAS) and per protocol (PP), where FAS refers to the data set obtained after minimal and fair removal of data from all randomized subjects. PP is sometimes referred to as “valid case” and “valid sample” and is a subset of the total analysis set. The subjects had sufficient adherence to the protocol to be able to estimate the effect of the treatment.

The PP population will include random patients in the ITT group but will exclude patients who do not meet the inclusion or exclusion criteria and randomly assigned patients who do not receive the actual treatment [33].

If the statistical results are the same, ITT and PP are reliable indicators. ITT results will be used if statistical evaluations are different between the two methods. As the final observation result (last observation carried forward), the missing data will be processed. The last observation value of the endpoint will be regarded as the follow-up evaluation point of missing data, and the last observation reaction will be regarded as the endpoint of the study.

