### Primary and secondary outcomes

In this study, the TIS will be the main observation index. At the same time, the clinical effect will be divided into three grades to evaluate the curative effect before and after treatment: complete response (CR), partial response (PR), and no response (NR). The results of this observation index will be defined as ranked data.

The secondary outcome measurements will include other relevant evaluation indicators, such as FMA, BBS, ADL, MPT, Dynamic and Static Balance Function, Diaphragm Thickness, and muscle mobility of the diaphragm. The data obtained from these indicators will be measurement data.

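### The outcome, sample-size and analysis sections do not agree on one primary test of the CR/PR/NR grades; the sample size supports only the effective-rate comparison

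*Protocol article*

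**What the plan says.** Four statements in the protocol article bear on the primary analysis.

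- **Primary and secondary outcomes.** TIS is the main index and is graded CR, PR or NR. Of this index the section says: "The results of this observation index will be defined as ranked data". Primary outcome measurement procedures sets the cuts: a gain of 7 or more is CR and a gain of 3 to 6 is PR.
- **Sample size calculation.** The inputs are two rates: "The effective rates of the study group and the control group were set as 80% and 50%, respectively". The test is given as rank-sum: "the rank-sum test was adopted to set the rates of 80% in the treatment group". The calculation is two-sided at the 5% level with 97% power, and the result is 71 per arm before attrition.
- **Statistical analysis, main test.** "The chi-square test will be used to compare differences in efficacy between groups". The three levels are to be expressed as rates or percentages. A rate is then defined, "Effective = (excellent + effective)/total cases × 100", with labels that are not the CR/PR/NR of the outcome section.
- **Statistical analysis, adjusted model.** A stepwise logistic regression is to deal with intervention time, stroke type, age and gender. Baseline TIS is not in that list.

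The t tests in the same section are for the secondary indicators. No between-group comparison of the TIS total as a score is described.

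**The concern.** The three sections describe different analyses. Ranked data and a rank-sum test imply an ordered comparison of three grades. A chi-square test on three grades ignores their order. A chi-square test on the effective rate merges CR with PR. The stepwise logistic model gives a further result for the same outcome, with covariates chosen by the data.

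These tests answer different questions and need not agree on one data set. If the choice stays open until outcomes have been seen by arm, the primary p-value can be selected and no longer carries its nominal 5% error. The exposure is real here: only the assessors are blinded (Blinding), and Monitoring provides for results to be available midway through the trial.

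**Working it through.** **1. The plan's own figure.** Inputs from Sample size calculation: p1 = 0.80, p2 = 0.50, two-sided alpha 0.05 (z = 1.960), power 0.97 (z = 1.881), ratio 1:1. The pooled rate is 0.65.

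n per arm = [1.960 × √(2 × 0.65 × 0.35) + 1.881 × √(0.80 × 0.20 + 0.50 × 0.50)]² / 0.30²
= [1.960 × 0.6745 + 1.881 × 0.6403]² / 0.09
= 2.526² / 0.09 = 70.9, so 71.

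This matches the stated 71 exactly, and power at 71 per arm is 0.970. Variants fit less well: continuity-corrected 78, unpooled 67.2, one-sided 60. Fisher's exact test at 71 per arm has power 0.955. A rank-sum size for three grades would need a split between CR and PR in each arm, and the protocol gives none.

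**2. Can the tests disagree?** Take 71 per arm with NR/PR/CR of 21/25/25 (study) and 33/22/16 (control).

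- Three-grade chi-square, arms equal: Σ(a − b)²/(a + b) = 144/54 + 9/47 + 81/41 = 4.83 on 2 df, p = 0.089.
- Effective rate, 50/71 v 38/71: 142 × (50 × 33 − 21 × 38)² / (71 × 71 × 88 × 54) = 142 × 852² / 23,954,832 = 4.30 on 1 df, p = 0.038. With a continuity correction, 852 becomes 852 − 71 = 781, the statistic is 3.62 and p = 0.057.
- Rank-sum with tie correction: U = 25 × 33 + 25 × (33 + 22) + ½ × (21 × 33 + 25 × 22 + 25 × 16) = 3021.5, against 71²/2 = 2520.5 under the null. The variance is (71²/12) × [143 − 330,066/(142 × 141)] = 53,147. So z = 501/230.5 = 2.17, p = 0.030.

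**3. Cost of choosing afterwards.** In simulations under the null (4,000 runs per setting, 71 or 80 per arm, assumed TIS distributions), each test alone rejected 4.4 to 5.4% of the time. Taking the smallest p of the three rejected 7.8 to 8.9%.

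**4. Power at the planned 80% v 50%, 71 per arm.** The effective rate has 0.97 whatever the CR/PR split. The other two depend on the split, which has to be assumed.

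| Assumed grades NR/PR/CR (%) | Three-grade chi-square | Rank-sum |
|---|---|---|
| 20/60/20 v 50/30/20 (CR equal) | 0.97 | 0.76 |
| 20/50/30 v 50/31/19 | 0.94 | about 0.92 |
| Normally distributed gain | about 0.98 | about 0.99 |

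In the equal-CR case the three tests disagree on significance in about 22% of trials.

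**5. The unused score.** The protocol gives no SD for TIS, so a normal gain with equal variances is assumed here. For a 0.5 SD effect at 70 per arm:

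- t test on the gain: noncentrality 0.5 × √35 = 2.96, power 0.84.
- Effective rate: 50% in control becomes Φ(0.5) = 69.1%, pooled 59.6%. Power = Φ[(0.191 × √70 − 1.960 × 0.694)/0.681] = Φ(0.355) = 0.64.

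The 0.84 is for an unadjusted t test, not for ANCOVA. In a separate simulation at half the planned shift (about 66% v 50%, 71 per arm, residual SD 2 to 4), the graded tests had power 0.45 to 0.59 and ANCOVA with baseline 0.68 to 0.82.

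**The case against.** The strongest reply is that Statistical analysis names one unadjusted between-group test for the grades, chi-square. Rank-sum occurs only in the sizing, and the effective rate is a formula with no test attached. A statistical analysis plan not shown here could settle the table. Also, on a two-category outcome the tie-corrected rank-sum is nearly the chi-square test (the statistics differ by a factor of 141/142), so the sizing label may be loose wording. All of this is fair and narrows the point. It does not remove it: the outcome is declared ranked, the named test ignores rank, the table is not fixed, and the sizing fits only one of the readings.

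A reader might infer more than the protocol supports:

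- **That the trial is underpowered.** It is not, on its own assumptions. The effective rate keeps 0.97, and efficiency is lost only if the effect is smaller than planned.
- **That chi-square is the weaker choice because it ignores order.** Rank-sum does worse in two of the three scenarios above.
- **That baseline is ignored.** The grades are built on change, so baseline enters by subtraction. What is missing is baseline TIS as a covariate.
- **That the ceiling spoils the endpoint.** With entry TIS of 6 to 17 and a maximum of 23, only a baseline of exactly 17 rules out CR (23 − 17 = 6, below 7). Such a patient can still be PR and count as effective.
- **That the graded endpoint must be replaced.** The grades appear consistently across the sections, and recruitment began in March 2018. Moving to the score is an efficiency option that would need a formal amendment.

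**Conclusion.** The point stands as an inconsistency over the primary analysis. The sections on outcomes, sample size and analysis do not identify one test of CR/PR/NR, and 71 per arm corresponds to the two-category effective rate. Leaving the choice among the three tests open would raise type I error to about 8 to 9%. That figure assumes the smallest of three p-values is taken, and it varies somewhat with the grade distribution. The example shows that the verdict can turn on the test, and even on a continuity correction.

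The sizing arithmetic is sound, and planned power is 0.97 for the effective rate. The gain from analysing the score (0.84 v 0.64 at 0.5 SD) rests on an assumed normal gain, since no TIS SD is given. It supports a recommendation to add that analysis, not a finding that the planned endpoint is invalid.

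**What to change.** 1. **Name one primary test** before anyone sees outcomes by arm, including at the midterm look, and record the date. The simplest is the effective rate, CR+PR v NR, by a two-sided chi-square test without continuity correction, which is what 71 per arm supports. Define it as a TIS gain of 3 or more and use the CR/PR/NR labels throughout.
2. **Correct the rank-sum wording** in Sample size calculation to a comparison of two proportions. Make the ranked-data statement in the outcomes section consistent with the chosen test.
3. **Replace the stepwise model** with a prespecified logistic model with arm and baseline TIS, marked as supportive. If the three grades are to stay primary, use a proportional-odds model with the same terms. It uses order much as rank-sum does, so it may share the power loss seen when the arms differ only between NR and PR. The sample size would then have to be restated with an assumed CR/PR split.
4. **Add week-2 TIS total by ANCOVA** with arm and baseline TIS, giving the mean difference and 95% CI, as a key supportive analysis. It could become primary only by formal amendment with the sample size restated.

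Cost: a small amendment, submitted in writing to the ethics committee as the Ethics section foresees. No new data or patients are needed. The headline then rests on one prespecified result, and the other analyses cannot replace it.

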## Methods/design

### Trial design

This study will be a single-center randomized controlled trial (RCT) in which 160 stroke patients will be randomly divided into study and control groups. The study will be conducted at Shanghai Xuhui Central Hospital between March 1, 2018, and March 31, 2021. The study will recruit eligible subjects from the inpatient and outpatient departments of rehabilitation medicine of Shanghai Xuhui District Central Hospital in Shanghai. Patients will be allocated in a 1:1 ratio to the study group or the control group. LQG combined with conventional rehabilitation will be completed by patients in the study group, whereas traditional core stability training combined with conventional rehabilitation will be completed by patients in the control group. The Trunk Impairment Scale (TIS) will be used as the main evaluation index. The secondary evaluations index will include the Fugl-Meyer Assessment (FMA), Maximum Phonation Time (MPT), Dynamic and Static Balance Testing (PK-254; TecnoBody, Dalmine, Italy), measurement of the thickness of the diaphragm, measurement of degrees of diaphragm mobility, Modified Barthel Index (MBI), and Berg Balance Scale (BBS). All assessments will be conducted at baseline, at 2 weeks, and at the end of the rehabilitation course. A flowchart of the study protocol is shown in Fig. 1. The research proposal has been designed according to the Standard Protocol Items: Recommendations for Interventional Trials (SPIRIT) 2013 statement recommendations (Fig. 2 and Additional file 1).

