### Primary outcome measurement procedures

Experienced physicians will assess the primary measures before and after treatment for 2 weeks. The TIS will be used to measure the main results (Table 1).

**Table 1 Tab1:** Specific measurement of trunk posture control levels carried out by Trunk Impairment Scale

	Baseline	2 weeks
Trunk posture control measurement		
Evaluation date		
Signature of therapist		

A main investigator will evaluate trunk postural control in the entry and exit stages. Trunk postural control measurement will be conducted according to the Spanish version of TIS 2.0. This scale consists of three subscales. The subscale of the first item is “static sitting balance” (score range 0–7) to assess the ability of patients to maintain sitting balance by landing on their feet and crossing their legs. The patient should cross the leg on the affected side. The second subscale will evaluate dynamic sitting balance (score range 0–10) and assess the lateral flexion of the trunk, starting from the upper and lower trunk. The third subscale will evaluate coordination (score range 0–6) and test the ability to independently rotate the shoulder girdle and pelvic girdle. The total scores will range from 0 to 23, with a higher score denoting better performance [19].

We will evaluate efficacy before and after the intervention According to the following criteria:

CR: TIS total score increased ≥ 7 points after treatment

PR: 3 points ≤ TIS total score increased ≤ 6 points

NR: total TIS score after treatment ≤ 2 points or worse

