### Limitations of the study

The limitations of the proposed study are as follows: (1) Due to the limited medical resources, patients are hospitalized only for a short period of time, with the intervention period of the study being only 2 weeks; (2) no follow-up investigation will be conducted after the intervention; (3) single- or double-blind observations will not be achieved; and (4) surface myoelectricity will not be used to test the activity of the trunk muscle group, and abdominal pressure test tools will not be used to reflect changes in abdominal pressure.

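### With TIS scheduled only at baseline and week 2, carrying the last value forward scores a missing week-2 patient as zero change (unless the analysis set excludes such patients), which conflicts with the sample size and can bias the primary comparison

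*Protocol article*

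**What the plan says.** The Statistical analysis section names last observation carried forward as the method for missing data: "The last observation value of the endpoint will be regarded as the follow-up evaluation point of missing data". It reports both ITT and per-protocol results and lets ITT prevail where they differ. The effective rate is computed over total cases and compared by chi-square. The section describes the full analysis set as what remains after a small, fair removal of data from the randomised patients, without saying which patients may be removed.

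On timing, Primary outcome measurement procedures says "Experienced physicians will assess the primary measures before and after treatment for 2 weeks". Table 1 has two columns, baseline and 2 weeks. Table 2 and Data management give the same two time points, and Limitations of the study says "no follow-up investigation will be conducted after the intervention". Trial design, however, says "All assessments will be conducted at baseline, at 2 weeks, and at the end of the rehabilitation course", and the Abstract repeats that third time point.

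A partial response needs a TIS gain of at least 3 points. The sample size section says "we set α = 0.05 and power = 0.97" and "the final sample size was set as 142, with 71 subjects in each of the two groups", then goes to 80 per arm, "taking into account the possibility of 12% attrition rate during the study".

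**The concern.** Carrying a value forward needs an intermediate post-baseline value. On the two-visit schedule a patient without a week-2 TIS has only the baseline. The rule then amounts to baseline carried forward: a gain of 0, which is neither a complete nor a partial response, with the patient kept in the denominator. The protocol does not say that this is what its rule does.

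Two things are at stake:

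- **Power.** The sample size assumes that dropouts leave and that the remaining patients show 80% v 50%. The analysis rule keeps dropouts in as failures, which shrinks both rates.
- **Bias.** If dropout differs between arms, the rule turns that difference into a difference in response. This is possible here because only assessors are blinded and patients are told their assignment by telephone.

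Zero change is also hard to defend on the protocol's own figures, since the sample size expects half of the controls to respond within two weeks.

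**Working it through.** **Inputs** (Sample size calculation unless noted): effective rates 80% and 50%, two-sided alpha 0.05, power 0.97, 71 evaluable and 80 randomised per arm, 12% attrition. The response threshold is a gain of 3 points (Primary outcome measurement procedures). The test is chi-square over total cases (Statistical analysis).

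**1. The protocol's figure reproduces.** With mean rate 0.65, the pooled two-proportion formula gives

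n = [1.960 × √(2 × 0.65 × 0.35) + 1.881 × √(0.80 × 0.20 + 0.50 × 0.50)]² / 0.30² = (1.322 + 1.204)² / 0.09 = 70.9, so 71 per arm.

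Exact power of the chi-square test at 71 per arm is 0.971. The allowance also reproduces: 142 × 1.12 = 159.04, raised to 160.

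**2. Dropouts left out, as the sample size assumes.** 80 × 0.88 = 70.4, about 70 per arm at 80% v 50%. Exact power is 0.968.

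**3. Dropouts kept at zero change, 12% in each arm.** This assumes that dropout is unrelated to response, so each rate is multiplied by 1 minus dropout:

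- Study: 0.80 × 0.88 = 0.704
- Control: 0.50 × 0.88 = 0.440
- Difference: 26.4 points instead of 30

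With mean rate 0.572 and 80 per arm:

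z = [0.264 × √80 − 1.960 × √(2 × 0.572 × 0.428)] / √(0.704 × 0.296 + 0.440 × 0.560) = (2.361 − 1.371) / 0.674 = 1.468

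Power is 0.929 (normal) or 0.924 (exact). About 100 per arm would be needed for 0.97. At other equal dropout rates, normal-approximation power is 0.966 (5%), 0.941 (10%), 0.908 (15%) and 0.867 (20%).

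**4. Unequal dropout, no true effect.** The protocol gives no split by arm, so these splits are assumed, with mean dropout 12%, a true response of 65% in both arms, 80 per arm and the exact chi-square test.

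| Dropout, one arm / other arm | Rates after carrying forward | False-positive rate |
|---|---|---|
| 12% / 12% | 57.2% v 57.2% | 4.7% |
| 10% / 14% | 58.5% v 55.9% | 5.9% |
| 8% / 16% | 59.8% v 54.6% | 9.6% |
| 6% / 18% | 61.1% v 53.3% | 16.2% |
| 5% / 19% | 61.75% v 52.65% | 20.5% |

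**5. Unequal dropout, true 80% v 50%.** Same assumed mean of 12%, exact power at 80 per arm.

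| Dropout, study / control | Rates after carrying forward | Difference (points) | Power |
|---|---|---|---|
| 18% / 6% | 65.6% v 47.0% | 18.6 | 0.65 |
| 14% / 10% | 68.8% v 45.0% | 23.8 | 0.86 |
| 12% / 12% | 70.4% v 44.0% | 26.4 | 0.92 |
| 10% / 14% | 72.0% v 43.0% | 29.0 | 0.96 |
| 6% / 18% | 75.2% v 41.0% | 34.2 | 0.99 |

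The true difference is 30 points in every row. The rule can understate or overstate it.

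**The case against.** **The analysis set may exclude these patients.** A reader might infer that every dropout is certain to be scored as no response. The text does not settle that. If the undefined removal step takes out patients without a week-2 score, nothing is carried forward for the TIS and power is about 0.97 (0.968 at 70 per arm). The protocol also speaks of TIS measurement at entry and exit without saying whether early leavers get an exit score. This stands, and the point is conditional on it. It does not rescue the rule, which would then have no TIS value to act on.

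**There may be a later visit.** If the third time point in Trial design were a separate endpoint visit, some dropouts would carry a week-2 value. The tables, Data management and Limitations make that the less likely reading, but the passages need reconciling.

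**The power loss is moderate and depends on direction.** A reader might infer that power always falls below 0.97. It does not: at 6% study / 18% control it is 0.99. At an equal 12% it stays above 0.92, which would seldom change a trial's conclusion. This stands. The gain in power in that row comes from an exaggerated effect, so it is no defence of the rule.

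**The largest false-positive rate is an extreme case.** The 5%/19% split is nearly fourfold and no document figure supports it. Both arms receive active training of equal length for only two weeks, so a large imbalance is not to be expected. This stands, and the 20.5% should be read only as the end of a range.

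**Counting missing as failure is a recognised convention** for responder outcomes, and imputation from baseline data alone recovers little and relies on missingness at random. This is fair, but a convention should be chosen and stated, and the sample size should follow it.

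Two further inferences are not supported. The documents do not show that these patients usually keep recovering; the argument needs only the protocol's own 50% control response. Nor do they show that the rule makes confidence intervals too narrow: where missing is defined as failure, nothing is imputed.

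**Conclusion.** The concern holds with moderate confidence, on the condition that patients without a week-2 TIS remain in the analysis set. In that case the stated rule is baseline carried forward and conflicts with the sample size. At the protocol's own 12%, equal in both arms and unrelated to response, the difference falls by 3.6 points and power is about 0.92 to 0.93 instead of 0.97.

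The potential for bias under unequal dropout is the stronger ground, but its size rests on assumed splits: little or no inflation of the false-positive rate near balance, and substantial inflation only when dropout differs widely. The direction cannot be predicted from the documents. This should be corrected before analysis. It does not make the trial uninterpretable.

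**What to change.** 1. Replace carrying forward for the primary TIS outcome with multiple imputation of the week-2 score on all randomised patients, using arm, baseline TIS, age, sex, stroke type and time since stroke. Derive the response grade from the imputed score.
2. Keep missing counted as no response as a labelled sensitivity analysis.
3. If that rule is to remain the main analysis, say so openly and restate the power as about 0.92 to 0.93 at 12% dropout in each arm.
4. State which randomised patients, if any, may be removed from the full analysis set, and whether those without a week-2 score are among them.
5. Reconcile the third time point in the Abstract and Trial design with the two-visit tables, so that the endpoint visit is fixed.

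The cost is revised wording and a little more programming, with no new visits, data or patients. The downside is a missing-at-random assumption that the data cannot confirm; the sensitivity analysis shows how far the result depends on it.
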